**Fig. 2 Fig2:**
[figure not shown]
Method for measuring occlusal-vertical dimension (OVD) using a probe with markings at 1, 3, 6, and 9 mm

Plaque [33] and gingival bleeding indices [34] will be recorded on the treated tooth as well as obtained by averaging the measurements from seven index teeth [22] (Table 4).

**Table 4 Tab4:** Evaluation criteria for the assessment of plaque index [33] and gingival health [34]

Plaque index scores [33]	• 0: no plaque • 1: thin visible plaque, difficult to identify • 2: thick visible plaque, easily detected.
Gingival health scores [34]	• 0: Normal: the gingival tissue appears firm, with pinkish or pale pink and opaque surface, with thin margins and variable degree of stippling. Contact with millimeter probe show its firmness • 1: slight inflammation: the gingival margin has slight change of color (reddish or bluish red) and is slightly swollen. Does not bleed after gentle probing • 2: moderate inflammation: the gingival tissue has become swollen (rounded edge, or bright red/blue). There is bleeding after gentle probing; 3: severe inflammation: the gingival tissue has markedly red or bluish red, swollen and enlarged, with ulcerations. Tendency to spontaneous bleeding

For the assessment of changes in DMFT/dmft, the same criteria for the evaluation of caries presence used at the baseline evaluation will be used [25] and the DMFT and dmft will be recorded [26].

An incremental cost-effectiveness ratio (ICER) will be calculated. The average cost per treatment will be quantified for both ART and the HT. Effectiveness will be measured by percentage of treatment survival. A microcosting will be carried out to estimate the direct costs of treating children with ART or the HT. This will include the capital costs of all equipment and instruments, materials and overheads, and the costs of time and labor. Additionally, the procedures will be timed using a stopwatch, started when the child has his/her mouth open and the operator is about to start the restorative intervention and stopped when the child stands up from the treatment table. The initial cost of treatments will be calculated, taking into account the parameters described in the Table 5. Therefore, the initial costs of treatments will be calculated by summing the expenses of capital cost, material cost and labor cost [35]. The ICER will be generated per treatment group by dividing the average initial cost by the survival after 3 years:

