**Table 5 Tab5:** Parameters used to calculate the costs per treatment

Capital cost	• Fixed cost of equipment and instruments such as the cost of autoclave and examination kits. For analysis we will assume that the lifespan of a dental instrument is approximately 3 years or 1095 days (constant depreciation rate).
Materials cost	• supplies such as gloves, masks, articulating paper, restorative material and PMCs. Their accumulated costs will be estimated per restoration.
Labor costs	• salaries of dentists and dental nurses delivering treatment will be calculated using the top point in their Brazilian Public health Service salary scales for the city in which the treatment is being provided. The labor cost per day will be divided by the number of restorations/ PMCs placed per day.

$$ ICER=\left({\mathrm{cost}}_i\hbox{-} {\mathrm{effectiveness}}_i\right)/\left({\mathrm{cost}}_c\hbox{-} {\mathrm{effectiveness}}_c\right)\;\mathrm{where}\;i=\mathrm{intervention}\;\mathrm{and}\;c=\mathrm{control}. $$

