#### Secondary outcomes

The Kolmogorov-Smirnov and Levene tests will be used to consider the normality distribution and homoscedasticity of the data, respectively. Depending on the data distribution, the Mann-Whitney test or *t* test will be applied to compare the degrees of discomfort, perception and concerns related to dental appearance reported by the child and their parents/caregivers; the child and their parent/caregivers’ reported acceptance of treatments among the two groups of intervention, as well as to evaluate the difference in mean scores of CPQ and P-CPQ among the two groups of intervention. The differences between the mean scores of the responses from the CPQ and P-CPQ questionnaire obtained at 1 month and at baseline will be calculated and tested, using a paired *t* test. The Friedman test will be used to compare the changes with regards to concerns related to dental appearance reported by the child and their parents/caregivers, changes in OVD; plaque index and gingival health. To evaluate the association between the secondary outcomes and children variables Ordinal Logistic Regression Analysis will be used. For cost-effectiveness analysis, the primary measure will be the survival rate of treatments. Therefore, as previously mentioned, the ICER will be generated per treatment group by dividing the average initial cost by the survival after 3 years:$$ ICER=\left({\mathrm{cost}}_i-{\mathrm{effectiveness}}_i\right)/\left({\mathrm{cost}}_c-{\mathrm{effectiveness}}_c\right)\mathrm{where}\;i=\mathrm{intervention}\ \mathrm{and}\;c=\mathrm{control}. $$

The significance level for all analyses will be *p* <0.05.

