In order to define public health care policies, costs of treatment have to be taken into consideration. Cost-effectiveness is defined as the analysis of costs of alternative treatments to be offered to a population [51]. Cost-effectiveness analyses have been used to appraise ART sealants and restorations in children and elderly populations [35]. The HT has been subjected to clinical evaluation in several studies [21–23, 46, 50], and one recent investigation addressed the results regarding the cost-effectiveness of three strategies for treating carious primary molars [52]. However, that study was a modeling design research and the economic evaluation of HT used in children has not yet been evaluated in a clinical trial.

In our investigation we aim to carry out an incremental cost-effectiveness evaluation where the initial costs of treatments (the costs to produce 1 unit of ART restoration or HT-crown) will be combined with the survival rates obtained by following the patients for 3 years. Therefore, we can calculate which treatment was initially cheaper to provide, but more importantly, what happened in terms of cost relative to the survival of restorations and teeth for each arm.

Understanding how people recognize the impact of oral health on their lives has become an emergent topic in the scientific community. With regards to dental caries, most research has been published on the impact of the disease and its consequences and little on the consequences of providing curative care on the population’s quality of life. There have been some investigations of changes in OHRQoL associated with ART [37, 53]. However, to date, no research has been carried out to investigate the OHRQoL associated with the use of the HT.

Evidence from this study will expand the body of knowledge around ART and the HT, two minimally invasive treatments growing in popularity. The findings will also inform public health policy decisions as well as clinicians’, childrens’ and parent/carers’ choices for primary molar occluso-proximal caries lesions.

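### Table 5's labour rule gives ART and HT the same unit labour cost on any day when both are treated, whatever time each takes, and does not attribute separator time to HT

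*Protocol article*

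**What the plan says.** The cost-effectiveness comparison is one of the listed secondary outcomes. The section on secondary outcomes evaluation plans a microcosting of direct costs that is to cover equipment, materials and overheads "and the costs of time and labor". The next sentence adds a time measurement: "Additionally, the procedures will be timed using a stopwatch, started when the child has his/her mouth open". The clock starts when the operator is about to begin the restorative procedure and stops when the child gets up from the table.

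The cost itself is the sum of the capital, materials and labour items defined in Table 5. For labour, Table 5 takes staff salaries and then states: "The labor cost per day will be divided by the number of restorations/ PMCs placed per day". Neither Table 5 nor the statistical analysis section refers to the stopwatch times.

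On delivery, the random allocation section assigns individual children, with the envelope opened once the child is ready for treatment. Table 2 describes HT in two steps: separators are fitted where there are contact points, and the crown is placed 3 to 5 days later. Table 6 lists separators for the HT arm only, at the baseline examination appointment.

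The cost horizon is declared. The discussion defines the cost as "the costs to produce 1 unit of ART restoration or HT-crown", and the statistical section describes the measure as "dividing the average initial cost by the survival after 3 years".

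**The concern.** The cost comparison asks whether one technique needs more resources than the other, and staff time is one of the resources on which they may differ. ART involves hand excavation, conditioning, filling and light curing. HT involves crown selection and cementation, often after a separator step. A rule that divides a day's labour by a count of treatments carries no information on how that labour was shared between the techniques. If both arms are treated on the same day, the labour component of the cost difference is fixed at zero by construction instead of being estimated.

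The separator step adds a second problem. It uses staff time for HT children only, but adds nothing to the count of restorations and crowns placed.

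At stake is the cost side of an economic result that the discussion offers to policy-makers. The primary survival analysis is not affected.

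**Working it through.** The article states no cost, time or cost-effectiveness figure, so there is nothing of its own to reproduce. The check is of what the rule implies.

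**Inputs from the article**
- Labour rule: day's labour cost divided by the number of treatments placed that day (Table 5).
- Individual randomisation, with no separation of the arms by day (random allocation section).
- Separators fitted for HT only, with no crown placed at that step (Tables 2 and 6).

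**Inputs assumed for illustration**
- Five ART and five HT on one day.
- Procedure times of 30 minutes (ART) and 20 minutes (HT), then a range of time ratios.
- A day's labour cost of L = 100 units.

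**Step 1: the rule on a mixed day.** With nA ART and nH HT treatments, each is charged L/(nA + nH). For five and five this is 100/10 = 10 for either technique. The labour difference is 0 for every possible pair of procedure times.

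**Step 2: allocation by time.** A treatment lasting t minutes is charged L × t/(nA × tA + nH × tH).
- Total minutes: 5 × 30 + 5 × 20 = 150 + 100 = 250.
- ART share: 150/250 = 60%, or 12 per treatment.
- HT share: 100/250 = 40%, or 8 per treatment.
- Difference, HT minus ART: 8 − 12 = −4, which is −40% of the rule's unit labour cost of 10.

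**Step 3: range.** For equal numbers per arm and time ratio r = tH/tA, the difference as a fraction of the rule's unit labour cost is 2(r − 1)/(1 + r).

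| HT/ART time ratio (assumed) | Labour difference, HT minus ART |
|---|---|
| 0.5 | −67% |
| 0.75 | −29% |
| 1 | 0 |
| 1.25 | +22% |
| 1.5 | +40% |
| 2 | +67% |

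The rule returns 0 in every row. It is right only where total staff time per child is equal.

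**Step 4: separator time.** In the 30 versus 20 minute example, a separator step averaging 30 − 20 = 10 minutes per HT child would equalise the arms. A longer one would reverse the direction. Under the rule, separator minutes either sit in that day's labour cost, and are then shared among whatever ART and HT treatments were placed, or fall on a day with no placements and are charged to nobody.

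**Step 5: the other reading of the divisor.** Suppose the slash in Table 5 means a separate divisor for each arm. On a five-and-five day both arms get 100/5 = 20, still equal, and 200 units are charged for 100 spent. On a day with six ART and four HT, the charges are 100/6 = 16.7 and 100/4 = 25. That difference comes only from the chance mix of allocations. This reading does not repair the rule.

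**The case against.** Several points on the other side have force.

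- **A condensed article may omit the link.** The stopwatch sentence directly follows the statement that time is a cost, and the costing follows a cited method that is not shown. The full protocol may connect them. So it is too strong to say that the times will go unused; the article states no use for them. But the labour rule is printed explicitly, and as printed it has no time term.
- **Mixed days are inferred.** The article does not say how treatments are scheduled, and on single-arm days the rule could let a difference through. Individual allocation makes mixed days likely, however, and nothing in the text prevents them.
- **HT may not need an extra visit.** Table 6 places separators at the baseline appointment, which both arms attend, and they are used only where there are contact points. The supportable claim is extra HT minutes for some children, not an extra visit for all.
- **Direction is unknown.** As the range above shows, timing could raise or lower HT's relative labour cost. This stands in full.

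A reader might also infer that costing only the initial placement is an error that favours the arm with more failures. The article does not support that. It declares initial cost as its measure in three places. Table 3 describes failed restorations and crowns as capable of being re-treated and does not say how often they will be. Failures already count against an arm through the survival divisor in the measure as the article words it. Costing retreatment to 36 months would answer a wider economic question, and leaving it out is a stated choice of scope.

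**Conclusion.** The point holds for the labour rule. As printed, Table 5 fixes the labour difference between ART and HT at zero on every mixed-arm day and does not attribute separator time to HT. This conflicts with the article's statement that time is costed and with its collection of procedure times.

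The conclusion rests on a literal reading of Table 5 and on some days having both arms. The size and sign of the error cannot be derived from the article: it gives no times, salaries or prices, and labour's share of total cost is also unknown. The 60:40 split is an illustration, not an estimate. The point affects one secondary outcome and is worth correcting because the data needed are largely being collected already. The printed ratio formula is a separate matter and nothing here depends on it.

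**What to change.** In Table 5, replace the daily division with labour cost per child = recorded minutes × staff cost per minute, summarised by arm. For HT children who receive separators, add the placement time. Time that step from now on, and apply the resulting average to children already treated. State in the text that this is how the stopwatch times enter the cost sum.

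Label the cost-effectiveness result as based on initial cost only. Retreatment costs may be added as a sensitivity analysis if the investigators wish; they are not needed to correct this point.

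The cost is small. The main procedure is already timed, so the only new measurement is the separator step. Recruitment is under way, so separator times not recorded at the time may be unrecoverable, and the average applied to earlier children should be reported as an approximation.

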### Follow-up examinations

At baseline, the outcome, child discomfort associated with treatment will be recorded:ART group: before and immediately after treatmentHT group (on two occasions): 1 – before and immediately after the placement of a separator when it is used, and 2 – before and immediately after the placement of the PMC

Perceptions and concerns related to dental appearance will be measured before and after treatment – for children and parents.

Questionnaires assessing acceptance of treatment will be given after treatment – for children and parents.

OVD measurement will be carried out before and after treatment.

Plaque index, gingival health, DMFT/dmft scores (before treatment) and the OHRQoL questionnaires will be recorded before treatment – for children and the OHRQoL questionnaire will be given to parents before treatment. Children will be assessed after 1 week, and then after 1, 6, 12, 24 and 36 months. At 1-week follow-up, the outcomes related to treatment evaluation, OVD measurement, plaque index and gingival health will be re-evaluated. At 1 month follow-up, the outcomes related to treatment evaluation, OVD measurement, plaque index and gingival health, DMFT/dmft scores and the questionnaire OHRQoL, will be re-evaluated. At other follow-ups (6, 12, 24 and 36 months), the outcomes related to treatment evaluation, OVD measurement, plaque index and gingival health, DMFT/dmft scores will be re-assessed (Table 6).

**Table 6 Tab6:** Sequence of procedures performed for each recruited participants

		ART group								HT group							
		Baseline		Evaluation						Baseline		Evaluation					
Event	Completed by	Baseline examination appointment	Treatment appointment	1 week	1 month	6 months	12 months	24 months	36 months	Baseline examination appointment	Treatment appointment	1 week	1 month	6 months	12 months	24 months	36 months
Consent/Assent	Dentist/Dental student	X								X							
DMFT/dmft	Dentist/Dental student	X			X	X	X	X	X	X			X	X	X	X	X
Plaque index	Dentist/Dental student	X		X	X	X	X	X	X	X		X	X	X	X	X	X
Gingival health	Dentist/Dental student	X		X	X	X	X	X	X	X		X	X	X	X	X	X
Instructions of oral hygiene/diet	Dentist/Dental student	X								X							
Orthodontic separators	Dentist/Dental student									X							
Treatment	Dentist/Dental student		X								X						
Wong-Baker faces scale (pre/post treatment)	Child		X							X	X						
Questionnaire about teeth appearance (pre/post treatment)	Child/Parent		X			X					X			X			
Questionnaire about acceptance in relation to treatment	Child/Parent		X								X						
Measurement of OVD	Dentist/Dental student		X*	X	X	X	X	X	X		X*	X	X	X	X	X	X
Perceptions regarding OHRQoL	Child/Parent		X		X						X		X				
Treatment evaluation	Dentist/Dental student			X	X	X	X	X	X				X	X	X	X	X

***OVD will be measured before and immediately after treatment during the treatment appointment in Atraumatic Restorative Treatment (ART) and Hall Technique (HT) groups

*DMFT/dmft* decayed, missing, filled teeth in permanent teeth/decayed, missing, filled teeth in primary teeth, *OHRQoL* oral health-related quality of life, *OVD* occlusal-vertical dimension

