### Primary outcome evaluation

One trained and calibrated examiner will carry out the follow-up evaluations. The examiner will undergo a training period according to the criteria adopted and in order to calculate intra-observer reliability, 20 % of the sample evaluated at the first evaluation period will be re-evaluated after 2 weeks. The intra agreement will be calculated and score above 0.7 will be accepted.

The treatments will be classified as “success” when they present as clinically satisfactory (that is where there have been no failures). Failures will be scored as “Minor Failures” and “Major Failures” (adapted from Innes et al., [21]). The Minor Failures will be those in which there is a defect in the restoration/crown, but it does not interfere with the tooth health. The Major Failures are when there are signs or symptoms of irreversible pulp damage, such as dental fistula/abscess, tooth fracture or failures that cannot be repaired (Table 3).

**Table 3 Tab3:** Evaluation criteria for the assessment of treatments (modified from Innes et al. [21])

Success	• satisfactory restoration/crown, no intervention required • no clinical signs or symptoms of pulp pathology • tooth exfoliated
Minor Failures	• secondary caries, or new lesions detected clinically • crown presents perforation • restoration fracture or wear - intervention required • loss of restoration - tooth that can be re-restored • crown loss - tooth able to be re-treated • reversible pulpitis, which could be treated without the need for extraction or pulpotomy
Major Failures	• irreversible pulpitis or dental fistula/abscess, requiring pulpotomy or extraction • loss of restoration/crown - tooth does not capable of being re-restored

The primary outcome of survival rate will be analyzed primarily as a composite of Minor and Major Failures but we will also conduct a further analysis by dividing the outcomes into two levels: assessment of treatment survival (Minor Failure) and tooth survival (Major Failure).

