### Statistical analysis

The inter- and intra-examiner reproducibility for assessing the primary outcome and secondary outcome OVD measurements will be calculated using a weighted Kappa test.

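### The examiner reliability check for the primary outcome is tied to the first (1-week) evaluation, when there are too few failures for kappa to be informative, and Table 6 omits that evaluation for the Hall Technique arm

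*Protocol article*

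**What the plan says.** **Schedule.** The Abstract (Methods/Design) and the Follow-up examinations section place evaluations at 1 week and at 1, 6, 12, 24 and 36 months for all children: "Children will be assessed after 1 week, and then after 1, 6, 12, 24 and 36 months". For the first of these visits the text adds: "At 1-week follow-up, the outcomes related to treatment evaluation, OVD measurement, plaque index and gingival health will be re-evaluated". Table 6, which that section cites, has a row "Treatment evaluation" with six marks for ART (1 week to 36 months) and five for HT (1 month to 36 months). The HT 1-week column is in use for OVD, plaque index and gingival health.

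**Reliability.** The Primary outcome evaluation section has one examiner and states that "20 % of the sample evaluated at the first evaluation period will be re-evaluated after 2 weeks" and that "The intra agreement will be calculated and score above 0.7 will be accepted". The Statistical analysis section begins "The inter- and intra-examiner reproducibility for assessing the primary outcome", extends this to OVD, and says that it "will be calculated using a weighted Kappa test".

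**The concern.** Treatment evaluation is the assessment that feeds the composite survival endpoint, so both arms need to be examined at the same visits. Text and table disagree on whether HT teeth are scored at 1 week, and staff may work from the table.

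The reliability check is meant to show that the examiner separates success from failure reproducibly. It can only do so on a sample that contains failures. One week after treatment there should be almost none, so the check could be carried out exactly as written and still leave the scoring of failures untested. The acceptance rule of 0.7 would then return no value, or would reject an examiner who agrees with himself or herself almost all of the time.

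The Statistical analysis section also promises inter-examiner agreement, although only one examiner is described.

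**Working it through.** **Inputs.** From Sample size calculation: ART survival 62 % at 2 years, absolute difference 25 %, hence HT 87 %; two-tailed alpha 5 %, power 80 %; 103 children, raised to 124. From Primary outcome evaluation: 20 % re-evaluated after 2 weeks, threshold 0.7. Assumed, because not stated: 1:1 allocation and a constant hazard in each arm.

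**The plan's own figure.** Hazard ratio = ln 0.87 / ln 0.62 = 0.291. Freedman's events = (1.960 + 0.842)² × ((1 + 0.291)/(1 − 0.291))² = 26.06. The mean failure proportion is (0.38 + 0.13)/2 = 0.255. Then 26.06/0.255 = 102.2, rounded up to 103, and 103 × 1.2 = 123.6, rounded up to 124. The figures reproduce, which confirms that 62 % and 87 % are the planning rates.

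**Table 6.** The row has 18 fields: 2 labels, 8 for ART and 8 for HT. ART has two blanks and then six marks. HT has three blanks and then five marks, the third blank being 1 week. All fields are present, so a lost column is unlikely.

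**Size of the schedule mismatch.** With t in years, F(t) = 1 − S^(t/2), where S is 2-year survival. At 1 week F is 0.0046 (ART) and 0.0013 (HT). Expected failures are 62 × 0.0046 = 0.28 for ART and 62 × 0.0013 = 0.08 for HT.

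**Failures available to the reliability check.** The sample is 20 % of 124 = 24.8, about 25 teeth. With the arms mixed equally, expected failures = 12.5 × (F_ART + F_HT), and P(none) = (1 − F_ART)^12.5 × (1 − F_HT)^12.5.

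| Time | F, ART | F, HT | Expected in 25 | P(none) |
|---|---|---|---|---|
| 1 week | 0.46% | 0.13% | 0.07 | 93% |
| 3 weeks (repeat scoring) | 1.36% | 0.40% | 0.22 | 80% |
| 1 month | 1.97% | 0.58% | 0.32 | 73% |
| 6 months | 11.3% | 3.4% | 1.8 | 15% |
| 12 months | 21.3% | 6.7% | 3.5 | 2% |
| 24 months | 38% | 13% | 6.4 | below 0.1% |

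If early failure is commoner than a constant hazard implies, P(none) at 1 week is 0.99^25 = 78% at a 1% rate, 0.98^25 = 60% at 2%, and 0.95^25 = 28% at 5%. It falls below one half at about 2.7%.

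**What kappa then does.** Kappa = (p_o − p_e)/(1 − p_e).

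- All 25 teeth scored as success twice: p_o = p_e = 1, and kappa is 0/0, undefined. Weighting does not help when only one category is used.
- One tooth scored as a failure on one occasion only: p_o = 24/25 = 0.96 and p_e = (24/25 × 1) + (1/25 × 0) = 0.96, so kappa = 0 with 96% raw agreement.

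Simulations with 25 teeth and two categories compared the failure rate expected at 1 week (0.3%) with that at 24 months (25.5%):

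| Failure rate | Examiner | Kappa undefined | Above 0.7 when defined | Raw agreement |
|---|---|---|---|---|
| 0.3% | error-free | 93% | all | 100% |
| 0.3% | sensitivity 95%, false positives 1% | 56% | 10% | 98% |
| 0.3% | sensitivity 95%, false positives 2% | 34% | 4% | 96% |
| 25.5% | sensitivity 95%, false positives 1% | 0% | 94% | 96% |
| 25.5% | sensitivity 95%, false positives 2% | 0% | 88% | 95% |

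The same examiner nearly always fails the threshold, or gets no value, at 1 week, and mostly passes at 24 months.

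**The case against.** **The blank cell is probably one omitted mark.** Two prose statements give 1 week for everyone, and Table 6 itself brings HT children in at that visit for other measures. This stands, and a typesetting or text-extraction slip cannot be excluded. A reader might infer that ART has its failures found earlier and that the survival comparison is biased. The documents do not support that: about 0.08 HT failures are expected by 1 week, and any that were missed would generally be found at 1 month in a 36-month comparison.

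**The plan does not name the visit for the reliability check.** True: 1 week is read from the schedule. If it meant 1 month, the chance of no failure would still be 73%. It is also tempting to say that the reliability sample holds no HT crowns. That does not follow, since under Table 6 the first HT treatment evaluation could be taken as the 1-month visit. An all-ART sample of 25 at 1 week would have an 89% chance of no failure, so little changes.

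**Kappa need not be undefined.** A reader might conclude that it usually will be. That requires a nearly error-free examiner; with 2% false positives it is undefined in about a third of runs. The supportable statement is that it is uninformative, by one route or the other.

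**Early timing has a purpose.** Agreement on OVD can be estimated at 1 week, an early check comes before most outcome scoring, and the examiner is also trained on the criteria. These points stand, and are reasons to keep an early check as well.

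**Masking.** One might add that the examiner is unblinded. Crowns and glass ionomer look different, but the article does not state whether the examiner is masked, so nothing here rests on it.

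**Conclusion.** The point holds in two parts of unequal weight. The text and Table 6 contradict each other on the 1-week primary-outcome evaluation in the HT arm. This needs correcting, with negligible direct effect on the log-rank test. The substantive defect is the placing of the reliability check. At the first evaluation about 0.07 failures are expected in 25 teeth, so the kappa rule cannot show that success and failure are scored reproducibly.

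This rests on the first evaluation being the 1-week visit, on a constant hazard from the planning rates, and on equal allocation. It weakens if early failure is well above 2.7%. It concerns the success/failure outcome only, not OVD. The inter-examiner wording is an inconsistency to clear up; it may refer to calibration against a reference rater, but the article does not say.

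**What to change.** 1. Reconcile Table 6 with the Abstract and the Follow-up examinations text, so that the primary outcome is examined at identical visits in both arms.
2. Keep the early re-evaluation for OVD. Move the 20 % primary-outcome re-evaluation to the 12- or 24-month visit, or repeat it there, sampling both arms (about 3.5 or 6.4 expected failures in 25). These counts are cumulative. If teeth that failed earlier have been repaired and no longer show as failures, the new failures since the previous visit are about 3.5 − 1.8 = 1.7 at 12 months and 6.4 − 3.5 = 2.9 at 24 months. That favours the later visit or oversampling of failed teeth.
3. State that both scorings are made on the tooth in the same state: both before any repair, or restricted to teeth not re-treated in between. This does not ask for any repair to be delayed. If repairs usually fall within the 2 weeks, the interval between scorings has to fit around them.
4. Report raw agreement with kappa.
5. Delete the reference to inter-examiner agreement, or say who the second examiner is and what he or she scores.

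**Cost.** One table cell, some wording, and a changed or second date for an examination that is already planned. The drawback is that primary-outcome reliability is known later, after some visits have been scored; repeating the check rather than moving it reduces that drawback.
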